#### Objective 2: data collection

We will use the RE-AIM framework to organize our assessment of implementation outcomes. We will focus on the following domains from RE-AIM, with additional attention to intervention acceptability [54].

##### (R) Reach

We will identify sub-populations that are best reached by the intervention and sub-populations who may benefit the most from the intervention. We will assess reach among enrolled participants in terms of actually fully receiving either ACF strategy. This will be determined through intervention logs and tracking tools.

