#### Objectives {7}

The overall purpose of TB aftermath is to compare the effectiveness, cost-effectiveness, and feasibility of two ACF strategies for detecting recurrent TB and provide evidence needed to implement and scale up the preferred ACF strategy. Our specific objectives are:To conduct a non-inferiority randomized trial to measure the comparative effectiveness of two potentially implementable ACF strategies within the NTEP, conducted by existing NTEP healthcare workers (HCWs): (i) home-based ACF (HACF) and (ii) telephonic ACF (TACF)To characterize implementation processes of the ACF strategies using the RE-AIM framework to inform their future scale-up and sustainability [54]To model the impact and cost-effectiveness of the ACF strategies evaluated in the trial, and of potential alternative strategies for the targeting and timing of those strategiesTo measure the association of the severity, chronicity, and progression of post-TB lung impairment with recurrent TB disease

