### Recruitment {15}

On a monthly basis, study staff will review NTEP registers to identify all potentially eligible participants nearing the end of their TB treatment at participating TUs. Patients for whom treatment was extended will also be tracked. All potential trial participants will be contacted and screened for enrolment with 60 days of treatment completion. For both index TB cases and HHCs who do not agree to participate, reasons will be documented and discussed by study staff. Accrual reports will be reviewed regularly and additional TUs will be added if required to achieve target sample size.

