##### Reach

We will use descriptive statistics to determine the proportions of socio-demographic groups that (a) receive the intervention as planned, and (b) are diagnosed with TB. We will use mixed effects logistic regression or log-binomial regression, including clinic as a mixed effect, to assess for associations between service receipt (e.g., home visit or telephone call) and the factors of interest. We will use mixed effects logistic regression to assess associations with recurrent TB diagnosis among the index patient and, separately, TB diagnosis among HHCs.

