##### Implementation

We will quantitatively assess indicators of implementation fidelity including (a) whether telephone contact numbers correct and available, (b) proportion of HHs respond to phone calls, and (c) proportion of HHs located and visited. We will use a goal of 90% delivery of components considered core and able to be controlled by the health system. If a lower level of delivery is achieved in any of these components, we will explore potential reasons in in the open-ended interview segment.

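### Reach is defined only among enrolled participants, so for household contacts it depends on a home visit that plays a different part in each arm, and for index patients it is delivery among the enrolled

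*Protocol article*

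**What the plan says.** Objective 2 (Objectives {7}) is to describe implementation "using the RE-AIM framework to inform their future scale-up and sustainability". Under Objective 2: data collection, (R) Reach, the protocol undertakes to identify which sub-populations are best reached, and then fixes the denominator: "We will assess reach among enrolled participants in terms of actually fully receiving either ACF strategy". The matching analysis section, Reach, will report "proportions of socio-demographic groups that (a) receive the intervention as planned" and names no wider denominator.

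How people become enrolled is set out elsewhere:

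- **Index patients.** Under Recruitment {15}, "study staff will review NTEP registers to identify all potentially eligible participants nearing the end of their TB treatment at participating TUs", and "For both index TB cases and HHCs who do not agree to participate, reasons will be documented and discussed by study staff". Neither the register list nor the refusals are linked to Reach.
- **Contacts.** Section {26a} places their consent at the first home visit. Footnote b of Table 1 says no study data come directly from contacts without a visit and consent.
- **HACF arm.** The health worker visits the home at 6 and 12 months.
- **TACF arm.** The index patient is telephoned at 6 and 12 months and also answers for the contacts. A home visit follows only if TB is suspected in someone.
- **Both arms.** Every household is visited at month 18 under the mop-up campaign.

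**The concern.** Reach is meant to tell the programme how much of the target population each strategy covers and which groups it misses. A denominator of enrolled participants contains only people whom study staff have already located, contacted and consented.

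The difficulty is sharpest for contacts. In HACF, the event that puts a contact into the denominator is also the event that delivers the screen. In TACF, the early entrants are contacts in households where TB was suspected, and the rest enter at month 18, after the strategy has finished. The two arms would be compared on contact groups formed by different processes, only partly independent of the outcome being measured.

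For index patients the problem is milder. Treatment completers who could not be contacted, or who declined, before enrolment never enter the denominator, so a group that is hard to find or reluctant at that stage cannot show up as poorly reached. Planners could read the result as population coverage when it is delivery among the enrolled.

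**Working it through.** The document gives no reach figure to reproduce. It also does not state the share of eligible patients who enrol, the share of contacts met at a visit, or the share of TACF households visited before month 18. The numbers below are illustrations under stated assumptions.

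**1. Index patients**

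Let e be the enrolled share of eligible completers (assumed), r the delivery among the enrolled, and q the delivery the non-enrolled would have had (unknown, 0 to 1). Coverage of all eligible = e·r + (1 − e)·q. Take r = 0.90, borrowed from the Implementation analysis section ("We will use a goal of 90% delivery of components considered core and able to be controlled by the health system"). That is a component-level goal and only a stand-in for full receipt.

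| e | q = 0 | q = r | q = 1 |
|---|---|---|---|
| 0.60 | 0.60 × 0.90 = 54% | 90% | 54% + 40% = 94% |
| 0.75 | 67.5% | 90% | 92.5% |
| 0.85 | 76.5% | 90% | 91.5% |
| 0.90 | 81% | 90% | 91% |

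The 54%, 68% and 77% values (rounded) are lower bounds. The figure among the enrolled overstates coverage only if q < r, by at most 36 points at e = 0.60 and 9 points at e = 0.90. If q > r it understates by at most 4 points and 1 point respectively.

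**2. Contacts, HACF**

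Assume that 90% of homes are located, that a contact is present at each visit independently with probability 0.6, and that a contact who is met consents and is screened at the same visit.

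- Enrolled by month 18: 0.9 × (1 − 0.4³) = 0.842
- Screened at least once by month 12: 0.9 × (1 − 0.4²) = 0.756
- Screened at both rounds: 0.9 × 0.6² = 0.324

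| Receipt counted as | Among enrolled | Among all contacts |
|---|---|---|
| At least one screen | 0.756 / 0.842 = 90% | 76% |
| Both screens | 0.324 / 0.842 = 38% | 32% |

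The gap is 14 points on the looser measure and 6 points if fully receiving the strategy means both rounds. If only contacts enrolled by month 12 are counted, at least one screen is 0.756 / 0.756 = 100% whatever the presence probability. That shows the circularity directly.

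**3. Contacts, TACF**

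Three groups pull in different directions:

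- Contacts visited early because TB was suspected are reached by construction, which pushes the figure up.
- Contacts first enrolled at month 18 were screened, if at all, only through the index patient. Whether that counts as receipt is not stated, so they may count as reached or not reached.
- Contacts screened through the index patient but never met at home are outside the denominator although the strategy covered them, which can push the figure down.

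No direction can be assigned without further facts.

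**The case against.** The strongest reply is that overstatement is assumed and not shown. Declining an 18-month study with lung function tests and cost surveys is not the same as declining a programme call or visit, and non-enrolled people were never offered either strategy. This stands. A reader might infer from the 54%, 68% and 77% values that index-patient coverage is definitely overstated in both arms. The documents do not support that, because those values set q to zero.

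Multiplying delivery by the enrolled fraction would also mix research participation into strategy reach. Since enrolment precedes randomization, one common factor e would apply to both arms and the ratio e·r₁ / e·r₂ would equal r₁ / r₂. This stands too.

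A reader might also infer that everyone who cannot be found drops out. That holds only before enrolment. Patients lost afterwards stay in the denominator as not reached, and the Implementation analyses count correct telephone numbers, households answering, and households located and visited.

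Reach could be read as a household measure, since service receipt is exemplified by a visit or a call. Yet the text says enrolled participants, and contacts are enrolled as participants. On the household reading, contacts would have no reach measure at all.

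Finally, this is a condensed article, and a recruitment cascade may appear in the full protocol. The point does not rest on an omission, however. The denominator is stated, and the way contacts enter it differs by arm.

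**Conclusion.** The point holds in limited form. For contacts, reach among the enrolled is partly conditional on delivery in HACF, where it is likely overstated. Its direction in TACF is unclear, and the arms are not comparable on it. That conclusion needs only the consent and visit rules. The sizes (6 points for both screens, 14 for at least one) rest on the assumed presence and location probabilities. That most TACF contacts enrol at month 18 is an inference from the rule that earlier visits require suspected TB.

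For index patients, the figure is delivery among the enrolled. It may or may not overstate coverage of all treatment completers, and the protocol gives no enrolled share with which to narrow the range.

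Reach is a descriptive implementation outcome. Nothing here touches the primary non-inferiority comparison.

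**What to change.** 1. Label the present figure as delivery among enrolled participants.
2. For contacts, report reach by arm over all household members counted by the index patient at entry. The household socio-economic items already record the number of occupants, so subtract the index patient. Show screening through the index patient in TACF as its own category, separate from contacts screened in person. The secondary outcome already takes an index-reported denominator for children under 6, so the principle is not new to this trial.
3. For index patients, report beside Reach the cascade from register-eligible to contacted, consented and fully screened. Compare non-enrolled with enrolled patients on whatever register variables are available. Do not present enrolled fraction times delivery as a point estimate of reach.

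The cost is analysis wording and tabulation of counts from registers already reviewed monthly, with no new procedure. Two limits remain. The document describes a count of occupants and names of children under 6 but no full household list, so contact reach by sub-group may not be possible for those never met. The resulting figure will also be less favourable and more qualified.

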##### (E) Effectiveness

The effectiveness of the two ACF strategies will be measured through our primary and secondary outcomes.

##### (A) Adoption and acceptability

We will assess adoption and acceptability using a mixed-methods approach. All interviews with index patients, HHCs, and HCWs will be conducted post final study visit (post 12-month endpoint) to ensure there is no contamination and to use 12-month outcomes for selecting participants. The interviews will be conducted by trained behavioral scientists fluent in local languages (Marathi and Hindi). The open-ended segment of interviews will be audio-recorded (with participant’s consent) and will be transcribed and translated into English as necessary. Our exploration of adoption and acceptability will be guided by a theory-based perspective using the Normalization Process Theory (NPT) [64–66]. Acceptability will be guided by the work of Sekhon et al. [67]. We will also explore perceptions of and experiences with the ACF strategies including (a) participant’s perceptions of alignment of services with needs, (b) confidentiality or other concerns with home visits, and (c) perceptions of the quality of services provided. The first component of the interview will include open-ended questions with probes, while the second half of the session will include structured survey questions on these domains.

##### (I) Implementation

Implementation will be assessed based on fidelity to the predetermined components, steps, and procedures of each ACF strategy quantitatively using intervention logbooks and tracking tools.

##### (M) Maintenance

The potential for maintenance will be assessed through the cost and cost-effectiveness analyses to be conducted in objective 3.

#### Objective 3: data collection

We will conduct a suite of economic evaluations and a modeling study based on empiric data collected during the trial. Figure 2 summarizes all economic cost data to be collected in the trial and data sources.

**Fig. 2 Fig2:**
[figure not shown]
Summary of major cost items and data sources

##### Time and motion studies

ACF operations will be assessed based on the WHO’s costing guidelines for TB interventions using an activity-based costing framework [68]. Cost data will be collated based on activities performed directly versus indirectly to the study participants and by resource type. Data on activity-based resource use will be assessed based on time and motion studies [69, 70]. These data will then be used to apportion program implementation costs, overhead costs, and infrastructural costs per patient screened and per patient diagnosed with TB. All resource use and cost data will be collected based on standardized cost data collection instruments [71, 72].

##### Health system and implementation costs

Costs will primarily be considered from the perspective of the NTEP as the party responsible for financing TB diagnosis and treatment in India. We will assess costs of implementing the intervention using a standardized, three-phase framework developed by our team [73]. For each implementation phase, we will collate resource-use and cost data for each pre-defined activity through periodic review of study activity reports/logs, financial documents, and discussions with study staff. Human resource time commitments will also be tracked for each study activity using a combination of study staff/HCW time sheets, activity logs, and structured interviews.

##### Patient costs

The WHO’s Tuberculosis Patient Cost Survey was designed as a cross-sectional survey and does not incorporate post-treatment costs [74]. TB Aftermath provides an opportunity to overcome these limitations by longitudinally surveying patients on costs experienced during and after TB treatment. Our modified survey also measures costs associated with the patient’s initial TB episode, any recurrence, and any new TB episodes among their HHCs. For index patients, pre-treatment and treatment phase costs will be assessed at study enrolment and post-treatment costs will be assessed at the months 6 and 18 (“mop-up”) time points. Specifically, we will measure wealth, changes in income and employment status, direct out-of-pocket costs of TB care, and borrowing and selling of assets to cope with illness during and after treatment.

#### Objective 4: data collection

We will measure lung function and respiratory health status at enrolment and month 18 (“mop-up”) in all participants and semi-annually in the home-based arm only. Lung function will be assessed by point-of-care pre-bronchodilator spirometry performed by trained study staff according to American Thoracic Society and European Respiratory Society guidelines [75]. We will collect key lung function indices such as forced expiratory volume in the 1st second (FEV1), forced vital capacity (FVC), and peak expiratory flow rate (PEF) at enrolment and follow-up. Additionally, we will measure respiratory health status and quality of life from the patient perspective using standardized questionnaires such as the Saint Georges Respiratory Questionnaire and the COPD Assessment Test [76–78].

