#### Intervention description {11a}

In both arms, ACF will be conducted by existing NTEP HCWs at 6 and 12 months after the index patient completes TB treatment. Based on the WHO and Government of India guidelines, the HCW will screen for any symptom of TB, including cough for ≥ 2 weeks, hemoptysis, fever, night sweats, weight loss, or lymph node swelling to screen for extrapulmonary TB [24, 56]. For participants with any symptom of TB, sputum specimens will be collected outside the home in the open air. As per routine programmatic conditions, sputa will undergo Xpert testing (or available microbiologic testing) and results will be returned to the patient.

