#### Relevant concomitant care permitted or prohibited during the trial {11d}

Participants may not be enrolled in another clinical study involving follow-up time points that conflict with TB Aftermath. However, clinical care may be sought at the participant’s discretion during the study period. Participants who report symptoms suggestive of TB disease will be referred to the TU for evaluation. Likewise, asymptomatic HHCs who are identified as potentially eligible for TPT per NTEP guidelines but who have yet to access services will be referred for further evaluation. Index patients newly diagnosed with diabetes at entry, and any participant with lung impairment will also be referred for appropriate care.

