### Outcomes {12}

#### Primary outcome

The rate per 100 person-years of people diagnosed with new or recurrent TB by study arm, within 12 months following index TB patient’s treatment completion date. TB disease will be diagnosed as microbiologically confirmed (positive acid fast bacilli smear or positive Xpert® MTB/RIF assays or positive culture) or clinically diagnosed (initiated on TB treatment with no microbiological confirmation) [57]. Primary analyses will be based on microbiologically confirmed TB cases among index patients (recurrent TB) or HHCs (new TB), and all analyses will be repeated including clinically diagnosed TB.

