**Household contacts**						
Informed consent and enrolment^b^		X	X	X		X
Clinical questionnaire		X^a^		X		X
Lung health assessments		X^a^		X^a^		X
TB symptom questionnaire		X	X	X	X	
TB event questionnaire		Any time TB case is identified				X

^a^Only among HACF arm participants

^b^Study data will not be collected directly from HHCs unless a home visit is conducted and they are consented

*Abbreviations*: *TB* tuberculosis, *WHO* World Health Organization, *HACF* home-based active case finding

The TB Aftermath study flow diagram is depicted in Fig. 1.

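### Study-staff lung and clinical assessments at months 6 and 12 are given to the HACF arm only; TB diagnoses they prompt enter the primary rate and cannot be told apart from the NTEP strategy's yield

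*Protocol article*

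**What the plan says.** **Strategies compared.** Objectives {7} and Intervention description {11a} define both arms as programme activities: "In both arms, ACF will be conducted by existing NTEP HCWs at 6 and 12 months".

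**Research assessments.** Objective 4: data collection schedules lung function and respiratory health status at enrolment and month 18 "in all participants and semi-annually in the home-based arm only". The work is "point-of-care pre-bronchodilator spirometry performed by trained study staff", and in addition "we will measure respiratory health status and quality of life from the patient perspective using standardized questionnaires". In Table 1, the footnote "Only among HACF arm participants" marks the index patients' lung assessments at months 6 and 12, the contacts' clinical questionnaire at month 6, and the contacts' lung assessments. The administration column gives all of these to study staff.

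**Referral.** Relevant concomitant care {11d} states: "Participants who report symptoms suggestive of TB disease will be referred to the TU for evaluation". It adds that "any participant with lung impairment will also be referred for appropriate care".

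**Endpoint.** The primary outcome is "The rate per 100 person-years of people diagnosed with new or recurrent TB by study arm", within 12 months of the index patient's treatment completion. The main analysis uses microbiologically confirmed cases and is repeated with clinically diagnosed cases added. The section on the mop-up campaign combines registry matching, questions at every contact and the month-18 visit so that all cases are counted, however they were found.

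**The concern.** The trial is meant to tell the programme what its own workers can detect by home visit and by telephone. In one arm only, a second team sees participants at the screening time points, asks about respiratory health and refers. If the NTEP worker's screen misses someone and the study-staff contact leads to a TU referral and a confirmed diagnosis within 12 months, that case is credited to HACF. Randomisation does not remove this, because the extra contact is assigned together with the arm.

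Two further results use the same counts. The first cost-effectiveness analysis rests on the primary outcome with costs mainly from the NTEP perspective, so a research-prompted case could count as yield with no programme activity behind it. The recurrence model is calibrated to the numbers detected at each screening visit by arm.

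**Working it through.** **1. What each arm receives from study staff after entry (Table 1; lung, clinical and cost items)**

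| Time point | Index, HACF | Index, TACF | Contacts, HACF | Contacts, TACF |
|---|---|---|---|---|
| Month 6 | lung assessment, cost survey | cost survey | clinical questionnaire, lung assessment | none |
| Month 12 | lung assessment | none | none | none |
| Month 18 | lung assessment, cost survey, clinical questionnaires | same | clinical questionnaire, lung assessment | clinical questionnaire |

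Month 18 lies outside the outcome window. Month 12 lies at its edge, so a work-up that starts there would mostly end outside it. The exposure that matters is essentially month 6. (Table 1's HACF-only mark on the contacts' month-18 lung assessment also disagrees with the Objective 4 text, which covers all participants then. This does not affect the primary rate.)

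**2. Inputs for the size (Sample size {14} and Statistical methods {20a})**

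- Per arm: 538 index patients + 1,076 contacts = 1,614 people; 10% loss; one year each.
- Rates: 12 (index) and 1 (contact) per 100 person-years (PY). Margin: 3 per 100 PY.
- 95% confidence interval, taken as one-sided 0.025.

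Person-years per arm = 1,614 × 0.9 = 1,453. Blended rate = (12 + 2 × 1)/3 = 4.67 per 100 PY. Expected cases per arm = 0.0467 × 1,453 = 68. One extra case = 1/1,453 = 0.07 per 100 PY.

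**3. The plan's own power figure**

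With equal rates, SE = √(2 × 0.04667/1,453) = 0.00802, and power = Φ(0.03/0.00802 − 1.96) = 96%, not the stated 80%. This is a separate matter. To stay close to the plan, the calculation is also calibrated to 80%. The size needed for 80% is 2 × 0.04667 × (1.960 + 0.842)²/0.03² = 814 PY per arm, so the implied design effect is 1,453/814 = 1.78. The article does not state a design effect; this one is only a calibration.

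**4. Effect of extra HACF-only detection**

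The documents give no yield for these visits, so x below is an assumed range. It takes the two strategies as otherwise equal, treats each extra case as one that would not have been diagnosed within 12 months anyway, and reads the margin as cases TACF misses. Power = Φ((0.03 − x)/SE − 1.96), with SE = √((0.04667 + x)/PY + 0.04667/PY). For example, x = 0.005 gives SE = 0.00823 and Φ(0.025/0.00823 − 1.96) = Φ(1.08) = 86%.

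| x per 100 PY | Extra cases (x × 1,453 PY) | Share of margin | Power, stated inputs | Power, calibrated to 80% |
|---|---|---|---|---|
| 0 | 0 | 0% | 96% | 80% |
| 0.2 | 3 | 7% | 93% | 74% |
| 0.5 | 7 | 17% | 86% | 62% |
| 1.0 | 15 | 33% | 66% | 43% |

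**5. Direction**

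Statistical methods {20a} requires the upper bound of the difference to lie below 3 but does not say which arm is subtracted from which. Extra HACF detection of x moves HACF minus TACF by +x, which makes the rule harder to meet. It moves TACF minus HACF by −x, which makes the rule easier to meet.

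**The case against.** The strongest reply is that these are not TB case-finding visits. Spirometry and respiratory questionnaires measure lung impairment, and impairment leads to referral for care, not expressly to TB testing. The TB symptom questionnaire belongs to the NTEP worker in both arms, who already acts on any symptom at the same time points. A research contact therefore adds a case only where that screen missed someone, and the main analysis requires microbiological confirmation. Symptom referral to the TU applies in both arms, and TACF index patients also meet study staff at month 6 for the cost survey. All of this stands. It limits the likely size, but the respiratory and contact assessments remain HACF-only and the symptom-referral rule applies at them.

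Part of the separation is already planned. The mop-up section distinguishes ACF-detected cases from others, and the cost-effectiveness outcome is per episode identified through the intervention. That two-way split does not say where a case prompted by study staff at an ACF time point belongs.

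A reader might infer that the contrast is really TACF against HACF plus a research case-finding programme, that TACF is certainly disadvantaged, or that reach and acceptability are inflated. The documents do not support these readings. No yield is given and the sign of the difference is open. Reach is taken from logs of ACF delivery, and added spirometry could as easily lower acceptability.

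A reader might also want these cases removed from the primary numerator, or the interim spirometry dropped. Removal would delete confirmed cases from one arm by unblinded attribution after randomisation, including some that would have been found anyway. Dropping the interim measurements would damage the Objective 4 analysis of change during follow-up and later recurrence.

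**Conclusion.** The point holds in a limited form. It is certain from the text that study-staff respiratory and clinical assessments at month 6, and for index patients at month 12, are confined to HACF, that referral rules apply at them, and that the primary rate counts a diagnosis whatever prompted it. Nothing in the article isolates the cases so prompted.

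The size is unknown. Under the assumed range of 3 to 15 wholly additional cases, the HACF rate rises by about 0.2 to 1.0 per 100 person-years, or 7% to 33% of the margin. Three cases would matter little; 7 to 15 would matter. If the margin means cases TACF misses, the effect works against TACF. With the opposite sign convention the stated rule becomes easier to meet. This is a weakness in attribution that can be repaired cheaply, and it does not invalidate the randomised comparison.

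**What to change.** - Leave the intention-to-treat primary numerator unchanged.
- At any shared time point, have the NTEP worker's symptom screen and any sputum collection completed and logged before a study-staff lung or clinical assessment begins. This orders the research procedures and leaves the referral rules as they are.
- Add a field to the TB event questionnaire for what triggered the work-up: NTEP screen, study-staff assessment, routine care or registry match.
- Pre-specify a sensitivity analysis of the primary comparison that excludes diagnoses triggered by study-staff month-6 or month-12 assessments, and apply the same exclusion to the cases credited to the intervention in the cost-effectiveness analysis. If attribution is accurate, the primary and sensitivity results bracket the HACF yield of NTEP workers alone.
- State the sign of the difference next to the decision rule, so that the direction of any shift can be read.

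The cost is one eCRF field, one order-of-procedures rule and one extra analysis. Attribution is made by unblinded staff, which is why the exclusion belongs in a sensitivity analysis. Recruitment began in January 2021 and was to run to about February 2023, so participants already past month 6 may lack the trigger field.
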